### Sample size

The sample size estimation is based on a minimal clinical important difference of 0.2 m/sec
^34^ between changes in gait speed among participants with highest performed exercise dose compared to participants with smallest performed exercise dose. Based on results from a pilot study leading up to this trial, we expect a maximal difference of 4 hours in performed exercise dose (total Time under tension summary dose) during the 7-week intervention period between participants with highest and lowest exercise compliance. Also based on the pilot study, a SD of 1.06 hours for exercise dose and 0.16 m/sec for change in gait speed were used. The power is set at 0.90 to increase the power for secondary analyses, and with a 0.05 level of significance. Based on the above, the required sample size is estimated to be 88 participants.

### Recruitment

The basis for recruitment makes the trial highly feasible due to the approximately 800 elective THA procedures performed annually at the Elective Surgery Centre. As there may be more eligible participants per day than for whom there is available equipment (BandCizers and ActivPAL sensors), we restrict inclusion by including consecutive participants from random sections of the department. That is, patients examined and booked for surgery in pre-specified clinics in the outpatient department. Patients are allocated to the specific clinics in the department by a secretary at random and with no influence from any personnel involved in the study. The estimated inclusion rate is approximately one to two participants per week; please see estimated participant flow and current recruitment status in
Figure 1.

**Figure 1. f1:**
[figure not shown]
Estimated participant flow.

### Blinding

The outcome assessors will be blinded to exercise compliance-data. Moreover, we will inform the participants that we measure how they perform their exercises and not how much they exercise or what the study hypothesis is. This is done with the purpose of minimizing sensor-induced influence on compliance and to reduce expectation bias.

### Data collection methods

The elastic band sensor (BandCizer) automatically records and stores exercise data during elastic band exercises. It is a valid measure of date, time of day, number of repetitions and sets, total time-under-tension (TUT), and total single repetition TUT during commonly used home-based strength training exercises for the lower extremities
^14^. The 40-m fast-paced walk test measures performance-based function and is part of the recommended core set of tests to assess physical function in people diagnosed with hip or knee osteoarthritis by the Osteoarthritis Research Society International (OARSI)
^26,
27^. A high inter-tester reliability is shown (intraclass correlation coefficient (ICC) 0.95) in a population with hip osteoarthritis
^34^. The HOOS questionnaire measures patient-reported outcome in the subscales: symptoms, pain, ADL, function in sport and recreation and hip-related quality of life
^28^. HOOS is shown valid, responsible, and reliable (ICC >0.78) when evaluating patients undergoing THA
^35^. Hip muscle strength
^29^ and 30-s chair stand test will be conducted in accordance with previous published methods
^27,
29^ showing acceptable relative and absolute inter-rater reliability when used after THA (ICC 0.83-0.93 and SEM 7–10%)
^36^. General Self-Efficacy Scale is a 10-item validated questionnaire holding a scale assessing optimistic self-beliefs to cope with a variety of difficult demands in life, scored between 1–4 points without any defined cut-off point
^30^. ActivPal movement-sensors measures physical activity as time spent in the sit/lie position (X-axis), standing (Y-axis) and walking (Z-axis). It has been validated in several studies in healthy adults
^37^ and in older adults with a hip fracture
^38,
39^.

Data collection will continue for participants who discontinue their training. Data collection will only be discontinued if participants explicitly withdraw from the study or any major events or diseases prevent the outcome assessments. If participants do not attend their scheduled follow ups, they will be contacted and offered a new time.

### Data management

Raw data from the Bandcizer will be uploaded to a secure online database using a tablet or smartphone. Here, the investigator will be able to access and analyze data and extract the following variables; date and number of training sessions, number of repetitions, time under tension for each repetition and total time under tension for each training session. Data from the outcome measurement will be double entered in EpiData 3.1 using anonymous coding with ID numbers and relevant range checks for data values to minimize typing errors. Completed data collection forms will be stored in a locked cabinet at Silkeborg Regional Hospital. Electronic data files will be stored on a secured hospital server with access requiring personal login. The linkage between ID numbers and personal identification data (e.g. civil registration number, name, address) will be stored as an electronic file as described above.

### Statistical methods

All the planned analyses are listed in
Table 3.

**Table 3. T3:** Variables, measures and methods of analysis.

Variable/outcome	Hypothesis	Outcome measure (unit, scale)	Methods of analysis
Demographic variables	Descriptive statistics, no hypothesis	Age, gender, height, weight, ASA status	Summary statistics
Supplementary descriptive variables	Descriptive statistics, no hypothesis	Prosthesis type, prior total joint replacement, length of hospital stay and self-efficacy (prior to surgery and baseline)	Summary statistics
Performed exercise dose of elastic band resistance training (exposure)	Descriptive statistics, no hypothesis	Time under tension summary dose/week and total (continuous) Number of exercise sessions/ week and total (number, continuous)	Summary statistics
1. Primary analysis			
Gait speed – measured by 40-m fast-paced walk test	Dose-response relationship	Change in score from baseline to follow up (meters/second, continuous)	(Described in more detail in section 2.12.1) Scatterplots of outcome variables and exercise dose variables will be used to suggest starting model structures and possible more complex alternatives. The analysis will depend on the specific relationship between change in gait speed and the exercise dose variable. Multiple models will be fitted and evaluated by R-squared values to identify the models that fit data the best. 1) The first model will be fitted as a fixed increase in outcome, based on exercise dose-change done by linear regression modelling. 2) If necessary, more complex regression, such as polynomial relationship and other nonlinear structures, will also be evaluated. 3) In the case that none of the models seem to fit the data, a linear regression model with a categorical variable based on intervals of the exercise dose variable will be fitted. If the measure at baseline correlates with the change, baseline measure will be adjusted for. The effect of possible confounding variables will be examined and, if having an effect, the confounder(s) will be adjusted for.
2. Secondary analyses			
HOOS ADL	Dose-response relationship	Change in score from baseline to follow up (points, continuous)	Similar to the primary analysis
HOOS symptoms, pain, QOL	Dose-response relationship	Change in score from baseline to follow up (points, continuous)	Summary statistics for the secondary outcomes will be presented as means with CIs or medians with IQRs within each of the compliance quartiles, and as graphical representation of these values as well.
30-s chair stand test		Change in score from baseline to follow up (repetitions, ordinal/continuous scale)	
Hip muscle strength (isometric)		Change in score from baseline to follow up (Nm/kg), continuous scale)	
3. Exploratory analyses			
Exercise compliance	Exploratory investigation of association. No hypothesis	Time under tension summary dose/week and total (continuous) Number of exercise sessions/ week and total (number, continuous)	Uni-variable regression models. Independent variables will be: pain flares (in the first two weeks of intervention and in the entire intervention period), HOOS pain (baseline), motivation to perform exercises, belief in effect of exercises, self-belief in compliance to exercising, satisfaction with rehabilitation exercise, physical activity (mean upright time/day and mean number of steps/day) and self-efficacy (baseline)
Physical activity level	Exploratory investigation of association. No hypothesis	Mean upright time per day (hours, continuous) and steps per day (numbers, continuous)	Uni-variable regression models. Independent variables will be: pain flares (first two weeks of intervention), HOOS pain (baseline), motivation to perform exercises, self-belief in compliance to exercising, and self-efficacy (baseline).
Result of the operation	Descriptive statistics, no hypothesis	Patient reported rating of perceived result after surgery (ordinal scale)	Data will be presented for each HOOS subscale (pain, symptoms, ADL, QOL) and gait speed. Data will be presented both for each response category, and for the subgroup of patients, who answered "excellent", "very good" or "good" data. This subgroup is considered to be reporting a hip-specific acceptable symptom state. Data will be presented by mean score with 95 % confidence intervals (CI) or median and inter quartile range (IQR). Furthermore, for each exercise dose quartile, the percentage of patients in each response category, will be presented (graphically). Finally, HOOS cut points for PASS will be estimated by the mean score or mean change approach
Change in hip problems	Descriptive statistics, no hypothesis	Patient reported rating of percieved problems in the operated hip now compared to before surgery (ordinal scale)	In each response category, the change in score from baseline to follow-up will be presented for each HOOS subscale (pain, symptoms, ADL, QOL) and gait speed. Data will be presented by mean with 95 % confidence intervals (CI) or median and inter quartile range (IQR). Furthermore, HOOS cut points for MCII will be estimated.
4. Other pre-specified outcomes			
Pain after exercise sessions	Descriptive statistics, no hypothesis	Change in pain per exercise session (score, continuous) Pain flare (increase in pain of ≥20 mm) during the first 14 days of the intervention (number, continuous) Pain flare for the entire intervention (number, continuous)	Summary statistics
Motivation to perform prescribed exercises	Descriptive statistics, no hypothesis	Motivation to perform exercises (ordinal scale) Belief in effect of exercises Self-belief in compliance to exercise	Summary statistics
Evaluation of prescribed exercises	Descriptive statistics, no hypothesis	Satisfaction with rehabilitation exercises Compliance with bandCizer Study-related change of exercise adherence	Summary statistics
Adverse events	Descriptive statistics, no hypothesis	Hip dislocation, infection, fracture, wound seepage, acute myocardial infarction, deep venous thrombosis, readmission, other)	Summary statistics

Descriptive analyses will be performed for demographic variables, supplementary descriptive variables, adverse events, motivation to perform prescribed exercises, evaluation of prescribed exercises and pain after exercise sessions (change in pain and pain flares). Data will be presented as means with 95% confidence intervals (CI) or medians with inter quartile ranges (IQR) for continues variables and as frequencies with percentages for categorical variables.

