## Methods

### Study design

The study is a pragmatic, single-center, prospective cohort study (single cohort) conducted in Silkeborg, Denmark. By pragmatic study we mean that the study reflects real life for the involved trial stakeholders. In this study this is for instance reflected by the type and dose of exercise which reflects our current practice. Outcome assessments will be performed at 3 (start of home-based strengthening exercise) and 10 weeks (after 7 weeks of home-based strengthening exercise) after surgery. Furthermore, patient-reported outcome measures will be collected pre-surgery (see the participant timeline in
Table 1). It is the aim that all outcome assessments will be performed by three physiotherapists who have been thoroughly trained in performing the outcome assessments. The data collection methods, trial logistics and the intervention have been tested in a pilot study including 10 patients and adjustments have been made accordingly. The study will adhere methodologically to the STROBE guideline for prospective cohort studies and the
CONSORT statement.

**Table 1. T1:** Participant timeline.

	Study period			
Time point	Admission	Baseline	Intervention	Follow up
	Pre or post surgery	3 week visit at the hospital	Week 3–10 post THA	10 week visit at the hospital
Enrollment				
Eligibility screen	X (pre)			
Informed consent	X (pre)			
Interventions				
Unloaded exercise	X (post) →			
Strengthening exercise		Exercise instruction	X	
Assessments				
Elastic band sensor (BandCizer)			X	
40-m fast-paced walk test		X		X
HOOS *	X (pre)	X		X
30-s chair stand test		X		X
Hip muscle strength		X		X
Pain: VAS ** at rest before + after exercise			X	
Self-reported additional exercises			X	
Self-efficacy	X (pre)	X		
Physical activity (ActivPal)			X (7 days data collection)	
Adverse events		X		X
Motivation to exercise as prescribed		X		
Evaluation of prescribed exercises				X
Change in hip problems				X
Perception of result after surgery				X

* HOOS: Hip disability and Osteoarthritis Outcome Score ** VAS: Visual Analogue Scale

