### Changes to outcomes after trial registration

At June 28, 2017, two outcome measures were added to the study. At 10 weeks after surgery, participants will be asked both to describe their perception of the result after surgery and the change in hip problems (from preoperatively to 10 weeks after surgery). The questions will be phrased as "How would you describe the result of your operation?" with response categories "Excellent", "Very good", "Good", "Fair", "Poor". The second question will be asked as "Overall, how are the problems now in the hip on which you had surgery, compared to before your operation?" with the response categories "Much better", "A little better", "About the same", "A little worse", "Much worse". These two questions have been used as anchor questions to establish patient acceptable symptom state (PASS) and minimal clinically important improvement (MCII) cut-points for patient-reported outcomes – including some subscales of HOOS – 1 year after THA
^32^. We will use these questions to group patients according to their perception of result of the operation and changes in hip problems, as well as for exploratory analysis of PASS and MCII cut-points for HOOS, 10 weeks after surgery.In April, 2019, pain flare was added as an outcome measure.Categories of adverse events were defined prior to study start, but they were not specifically described in the trial registration. Motivation to perform prescribed exercises was registered as outcome, but although predefined, the three items in the short questionnaire were not specifically described. Evaluation of prescribed exercises was added as outcome prior to study start.In April 2019, the secondary objective was added to the primary and pre-specified objective because the primary objective did not clearly outline the secondary analyses of secondary outcomes for the hypothesized dose-response relationship.All the changes outlined above occurred before the last participant was included and the study was unblinded (please see “Blinding” below).

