### Exploratory analyses

To better understand what may relate to how patients comply with prescribed rehabilitation exercise after THA, we will investigate how different variables relate to exercise compliance (dependent variables: time under tension summary dose and total number of exercise sessions), using uni-variable modelling. Independent variables will be: pain flares (first two weeks of intervention), pain flares (entire intervention period), HOOS pain (baseline), motivation to perform exercises, belief in effect of exercises, self-belief in compliance to exercising, satisfaction with rehabilitation exercise, physical activity (mean upright time/day and mean number of steps/day) and self-efficacy (baseline).

To better understand what may relate to how physically active patients are after a THA, we will investigate how different variables relate to physical activity (dependent variables: mean upright time/day and mean number of steps/day), using univariate modelling. Independent variables will be: pain flares (first two weeks of intervention), HOOS pain (baseline), motivation to perform exercises, self-belief in compliance to exercising, and self-efficacy (baseline).

In the analysis of "result of the operation", the change in score from baseline to follow-up will be presented for each HOOS subscale (pain, symptoms, ADL, QOL) and gait speed. Data will be presented both for each response category of the anchor question, and for the subgroup of patients, who answered "excellent", "very good" or "good" data. This subgroup is considered to be reporting a hip-specific acceptable symptom state. Data will be presented by means with 95% CI or medians and interquartile ranges (IQR). In each response category of the question for "change in hip problems", the change in score from baseline to follow-up will be presented for each HOOS subscale (pain, symptoms, ADL, QOL) and gait speed. Data will be presented by mean scores with 95% CI or median and inter quartile range (IQR).

Furthermore, for each exercise dose quartile, the percentage of patients in each response category of the questions for "result of the operation" and "change in hip problems", will be presented graphically. Finally, HOOS cut points for PASS and MCII will be estimated by the mean score or mean change approach
^40^.

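### The MCII anchor asks about change since before surgery, but the HOOS change tabulated against it starts 3 weeks after surgery; the PASS summary is contradictory

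*Protocol article*

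**What the plan says.** Two patient-reported questions at 10 weeks were added after registration, partly to explore PASS and MCII cut-points for HOOS.

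- **Change in hip problems (MCII).** Changes to outcomes after trial registration describes this as "the change in hip problems (from preoperatively to 10 weeks after surgery", and the item reads "Overall, how are the problems now in the hip on which you had surgery, compared to before your operation". In Table 3 the analysis is: "In each response category, the change in score from baseline to follow-up will be presented for each HOOS subscale". The same cell then says that MCII cut-points for HOOS will be estimated.
- **Result of the operation (PASS).** Patients rate the result on a five-level scale, and the top three levels define an acceptable symptom state. Table 3 summarises HOOS and gait speed by mean score or median. The Exploratory analyses text says instead that "the change in score from baseline to follow-up will be presented for each HOOS subscale (pain, symptoms, ADL, QOL) and gait speed".
- **Cut-point method.** The Exploratory analyses text names a mean score or a mean change approach for PASS and MCII together, without saying which serves which. Table 3 leaves the same choice open for PASS.
- **Timing.** Study design states: "Outcome assessments will be performed at 3 (start of home-based strengthening exercise) and 10 weeks". Table 1 heads the 3-week visit as Baseline and places pre-surgery under Admission. Study design adds that "patient-reported outcome measures will be collected pre-surgery", and Table 1 marks HOOS at that time. The walk test is marked only at 3 and 10 weeks.

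**The concern.** An anchor-based MCII is meaningful only if the anchor and the score cover the same interval. Here the anchor covers the operation and the recovery after it, while the score covers only the seven weeks of home exercise. A patient may answer *much better* because of the surgery and still show little HOOS change between weeks 3 and 10. The mean 3-to-10-week change among patients who say they are *a little better* is then not the change that the answer describes.

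PASS is a state, so the natural quantity is the score at 10 weeks. With table and text in disagreement, two analysts could follow the same article and report different thresholds.

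At stake is the interpretation of the exploratory cut-points. No hypothesis test in the study depends on them.

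**Working it through.** **No figure of the plan's own on this point.** The article gives no HOOS values. Its one related figure, N = 88, comes from gait speed only. Slope = 0.2/4 = 0.05 m/s per hour; r = 0.05 × 1.06/0.16 = 0.331; residual SD = 0.16 × √(1 − 0.331²) = 0.151. With a two-sided 5% test (sidedness assumed) and the noncentral t distribution, n = 88 gives power 0.903. The figure reproduces, and no HOOS quantity enters it.

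**Step 1: the two windows side by side.**

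- Anchor: before surgery to 10 weeks (Changes to outcomes after trial registration; repeated in the Table 3 row).
- Score: baseline to follow-up (Table 3; Exploratory analyses).
- Meaning of baseline: the 3-week visit (Table 1). Table 3 also lists self-efficacy before surgery and at baseline as two separate measurements, so baseline cannot be read as pre-operative.
- Other HOOS change windows: none. The secondary outcomes also use 3 to 10 weeks, and no listed analysis uses pre-surgery HOOS.

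**Step 2: what is omitted.** Let A be the change from pre-surgery to week 3 and B the change from week 3 to week 10. The anchor asks about A + B; the planned score is B. Within any anchor category,

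mean(A + B) − mean(B) = mean(A in that category).

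The error therefore equals the mean early change *among patients who gave that answer*, which can be positive, zero or negative.

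**Step 3: illustration, all values assumed.** B has mean 10 and SD 12; A has mean a and SD 15; the anchor is A + B plus noise of SD 10, all independent and normal. *A little better* is taken as the 10th to 25th percentile of the anchor.

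- Anchor variance = 225 + 144 + 100 = 469; SD = 21.66.
- Mean standardised anchor in the band = (0.1755 − 0.3178)/0.15 = −0.949.
- Mean B in the band = 10 − 0.949 × 144/21.66 = 3.7, whatever a is.
- Mean A + B in the band = a + 10 − 0.949 × 369/21.66 = a − 6.2.
- For a = 0, 10, 20, 30 the anchor-window mean is about −6, 4, 14, 24, against 3.7 throughout for the planned window.
- Correlation of the anchor with A + B = √(369/469) = 0.89; with B alone = 12/21.66 = 0.55.

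Under these assumptions the planned value is too high at a = 0, about right at a = 10, and too low at a = 20 or 30. Because the band is fixed by percentile, the individual values are not realistic estimates. The illustration shows only that the sign depends on a quantity the article does not give.

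**Step 4: PASS.** Table 3 gives mean score. The Exploratory analyses text gives change from baseline to follow-up. The two differ for the same analysis, and the cut-point method does not settle which applies.

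**Step 5: gait speed.** Table 1 has no pre-surgery walk test, so gait-speed change by the *compared to before surgery* anchor can only be 3 to 10 weeks and cannot be matched to it.

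**The case against.** **The MCII sentence names no window.** The baseline-to-follow-up wording governs the display by response category, and the MCII sentence comes after it. The authors state the anchor's interval correctly and hold pre-surgery HOOS, so they may intend the right window. This stands as a caveat on the cut-point itself. It does not rescue the display, which is mismatched as stated in both table and text, and no other change window is available to someone following the article. The article condenses a fuller protocol, but this is a stated pairing, not an omitted detail.

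**The MCII would be too small.** A reader might infer that it is understated by the whole improvement between surgery and week 3. The article does not support a direction. The Introduction says strength and functional performance are markedly lower early after surgery; that concerns performance, not HOOS, but it means early improvement cannot be presumed. If HOOS at week 3 were below its pre-surgery level in the anchor category, the error would reverse.

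**PASS would be built on change.** A reader might also infer this from the Exploratory analyses text. Table 3 says mean score, and the mean score approach remains open for the cut-point. What is established is a contradiction and an unassigned method, not a settled plan.

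**The analyses are exploratory.** Both rows are marked as descriptive without a hypothesis, and no gait-speed cut-point is planned. That stands, and it limits the severity.

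**Conclusion.** The mismatch for *change in hip problems* is real and can be read from the article: the anchor starts before surgery, and the HOOS change tabulated against it starts at week 3. An MCII estimated from the only change window defined would be biased by the mean early HOOS change in the anchor category. This rests on two readings: that baseline means the 3-week visit, which Table 1 fixes, and that the MCII uses the one change window defined, which is the likely reading but is not stated. Neither size nor sign can be given without HOOS data at both early time points.

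For PASS the fault is an internal contradiction and an unassigned choice of method. For gait speed it is a labelling matter.

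Severity is minor to moderate. The cut-points are exploratory, and the primary analysis and N = 88 are untouched.

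**What to change.** 1. In Table 3 and Exploratory analyses, present HOOS by the *change in hip problems* anchor as change from pre-surgery to 10 weeks, and state that the MCII is estimated from that change.
2. State that PASS cut-points use the HOOS score at 10 weeks. Make Table 3 and the text agree on this for *result of the operation*, and assign mean score to PASS and mean change to MCII.
3. Label gait-speed change by the *change in hip problems* anchor as 3 to 10 weeks and not aligned with the anchor's interval.
4. If the 3-to-10-week HOOS change by this anchor is still of interest, show it as a separate description and derive no MCII from it.

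The cost is wording only. Pre-surgery HOOS is already in the participant timeline, so no new data, visits or participants are needed.
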